#### Tertiary outcome measures

The tertiary outcomes include: the perceived consequences of falling (CoF) with two 6-item subscales ('loss of functional independence' and 'damage to identity') [9]; catastrophic beliefs about the consequences of a fall (CAFS: Catastrophising About Falling Scale, 5 items) [37]; perceived control over falling (PCOF; 4 items) [38]; mastery (7 items) [39]; feelings of anxiety and symptoms of depression with two 7-item subscales of the Hospital Anxiety and Depression Scale (HADS) [40,41]; social support interactions (SSL12-I: Social Support List of Interaction, 12 items) [42]; and health-related quality of life (SF-12: Health Survey, 12 items) [43].

#### Additional variables

Several variables are assessed to provide insight into the population under study, and to interpret the outcomes of the study. The socio-demographic and health-related variables, assessed during the process of screening for eligibility, are: age, gender, living alone or not, educational level, perceived general health (item one of the MOS SF-20) [23,44], and self-reported impaired vision and hearing [45]. Other health-related variables assessed during the baseline measurement are: chronic medical conditions (a 5-item checklist) [46] and cognitive status (AMT4: shortened version of the Abbreviated Mental Test; 4 items and TICS: Telephone Interview Cognitive Status; 11 items) [24,25]. Furthermore, 1-item questions on concerns about falls, the avoidance of activities owing to these concerns and the number of falls are assessed at baseline, as well as at all follow-up measurements. Lastly, at the baseline, participants are asked about their outcome expectations with regard to the programme [47].

### Process evaluation

To determine the feasibility of the programme and to identify factors that may influence its effectiveness, the following outcomes of the process evaluation are assessed: characteristics of the population reached (reach); protocol adherence by facilitators (fidelity); protocol adherence by participants (dose received: exposure); participants and facilitators' opinion about the programme and perceived benefits and achievements (dose received: satisfaction); and experienced barriers and potential solutions for these (barriers) [21,48,49]. Table 3 provides a detailed overview of the outcomes of the process evaluation and their operationalisation during the course of the trial. Data is collected from participants in the programme group, and from the facilitators.

**Table 3 T3:** Outcome measures of the process evaluation

Component and definition	Operationalisation	Measurement						
		SQ	QCf	V	Qf	Qp	If	D
**Reach**								
Proportion of the intended target population that participated in the programme	Characteristics of participants and facilitators	+						+
	Number of participants that refused, dropped out or completed the programme							+
	Reasons for withdrawal							+

**Fidelity**								
Extent to which the programme was implemented as planned	Preparation time and duration of the session		+	+				
	Per session component: extent to which carried out, duration and active participation by the participant		+	+				
	Extent to which the facilitator achieved to:							
	- conveying information to the participant			+	+			
	- having the participant phrase their important activities and how these activities could be performed safely and independently			+	+			
	- having the participant set goals regarding an action plan			+	+			
	- using motivational interviewing techniques			+	+			

**Dose received (exposure)**								
Extent of participants' active engagement in and receptiveness to the programme	Overall opinion of the facilitator/participant regarding the participant's engagement in:							
	- the programme				+	+		
	- the formulation of an action plan and carrying out an action plan				+	+		
	Use of materials		+			+		
	Exposure and adherence to homework		+		+	+		
	Extent to which the participant complied with contracts		+		+	+		
	Quality of action plans formulated by the participants				+	+		

**Dose received (satisfaction)**								
Satisfaction of participants and facilitators with the programme	Overall opinion of the participant					+		
	Experienced benefits, burden, usefulness by the participants				+	+		
	Recommendations to others by participants					+		
	Overall opinion of the facilitator				+		+	

**Barriers**								
The extent to which problems were encountered while applying the programme	Strong and weak aspects of the programme				+	+	+	
	Matters for improvement				+	+	+	

SQ = screening questionnaire filled in by participant before start programme, QCf = questionnaire filled in by facilitator for each participant for each contact, V = voice recording for selection of contacts, Qf = questionnaire filled in by facilitator for each participant after completion of programme, Qp = questionnaire filled in by participant after programme, If = group interview with facilitators, and D = data recorded by researchers during programme period

### Economic evaluation

A cost-effectiveness analysis is carried out in which costs are considered from a societal perspective. The economic evaluation measures and evaluates the 'real' costs. In this study, direct health-care costs are included; i.e. costs incurred by the in-home programme and health-care costs incurred by the participants. The costs of the programme consist of used materials, salaries of the facilitators, costs of training sessions for the facilitators etc. Health-care costs include hospital visits (inpatient and outpatient treatment), GP consultations, visits to paramedics, (nursing) home-care, informal care, and aids and appliances. In order to estimate the costs, the quantity of each resource will be multiplied by its assigned unit cost of price. Cost prices are obtained from the Dutch guidelines for cost analysis in health-care research [50,51]. If such guidelines do not provide for specific health-care use, real costs or tariffs will be used to estimate costs.

### Data collection

Data for the *effect evaluation *is gathered by means of telephone interviews which are conducted by trained interviewers, who are blinded for group allocation. For the assessment of fall accidents, participants received a fall calendar after the baseline measurement. Every month, a sheet of the calendar has to be returned via a freepost envelope. People are reminded by telephone after one-and-half weeks if a sheet is not returned.

The *process evaluation *data is gathered by several means. Participants who complete at least five sessions, fill in a questionnaire to report on the programme's feasibility and usefulness. Facilitators receive a registration form for each participant to report on the time spent per session, the participant's adherence with regard to homework assignments and the extent to which the programme is performed according to protocol. Voice recordings are used in a random selection of the sessions to gather objective data about the performance according to the protocol. Additionally, facilitators fill in questionnaires that assess their opinion about the programme for each participant and their overall opinion of the programme. Researchers conduct short telephone interviews to identify the reason(s) for withdrawal among people who do not complete the programme. Lastly, the researchers conduct a final evaluation meeting with the facilitators to discuss the overall programme.

The fall calendar mentioned before is also used for the collection of the data for the *economic evaluation*. Participants have to report their use of health-care services each month, in addition to their fall accidents.

Non-compliant participants of the programme group are approached for all follow-up measurements, and participants with missing data are contacted to ensure completion of data, as recommended by Hollis and Campbell [52].

Newsletters are sent 4 and 11 months after the baseline measurement, to keep the participants informed about the trial.

### Sample size and power

Sample size calculations are based on outcomes of a previous study using the Falls Efficacy Scale-International (FES-I) among older people in The Netherlands [53]. Two times 112 participants will provide 80% power at alpha 0.05 (one-tailed) to detect differences between the intervention and control groups' mean score of at least 3.8 points (SD is 11.4 equivalent with an effect size of 0.33 on the FES-I). However, a dropout rate of 20% during the study is expected, based on the experiences in the home visit study from Van Haastregt et al. [54]. Therefore, 2 × 140 participants are needed to enrol in the trial.

In a previous Dutch study, 54% of the population reported fear of falling, 38% reported related avoidance behaviour, and 48% reported poor or fair perceived general health [8]. Based on the experiences in that study and on the evaluation of AMB-NL [15], we estimate that approximately 6% of the older people who return the screening questionnaire will meet all inclusion and exclusion criteria and will be interested in participating in the trial. With an estimated response rate of 55%, a minimum sample of 8,200 older persons aged 70 or over needs to be approached with a screening questionnaire.

### Analysis

Descriptive techniques will be used to describe the study groups. Baseline variables will be compared, to detect differences between the participants of both groups at the start of the study. Data of the effect evaluation will be analysed according to both the intention-to-treat and per-protocol principles. In the first analyses all participants will be included according to their original assignment [52]. Participants of the intervention group who attended at least five of the seven programme sessions will be included in the per-protocol analysis. Based on prior work, five sessions of the programme are considered as sufficient programme exposure [15,18]. Mixed-effects regression analyses will be applied, to test for between-group differences with respect to the primary, secondary and tertiary outcome measures at all follow-up assessments. Models will be adjusted for the following covariates, considered as relevant for the outcomes [8]: concerns about falls, age, gender, perceived general health, and number of falls in the past 6 months at baseline. Additional covariates will be included in the analysis if baseline differences are detected for variables relevant for the outcomes. The level of statistical significance will be set at 0.05 (one-tailed). Data on the process and economic evaluation will be analysed and presented using descriptive techniques and appropriate statistical testing.

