## Background

Falls and concerns related to falls are very common in community-dwelling older people. About one in three older people living in the community experiences at least one fall each year, of which roughly half results in an injury [1,2]. Interestingly, around two-thirds of older people report concerns related to falls [3], of which roughly half report activity avoidance as a result of these concerns [4-8]. Concerns about falls can be present in both people who have fallen and people who have not [9]. These concerns have been linked to decreased balance performance, decreased mobility, functional decline, low quality of life, institutionalisation and falls [3,10-13]. Recent research has shown that concerns about falls can lead to falls irrespective of any physiological fall risk [13].

Concerns about falls can be considered as a multifactorial problem [14,15]. As a consequence, successful programmes should not only target concerns about falls but should also focus on aspects like increasing self-efficacy and a sense of control regarding the risks of falling, setting realistic goals for increasing activity, changing the environment to reduce the fall risk and promoting physical activity to increase strength and balance [15-19].

Cognitive behavioural therapy could be seen as a suitable strategy to reduce concerns about falls by modifying patterns of thoughts (cognition) and actions (behaviour) that contribute to the concern.

One of the programmes with proven effectiveness is the Dutch version of 'A Matter of Balance' (AMB-NL) [20]. This multicomponent cognitive behavioural group programme consists of eight weekly group sessions and a booster session after six months. It has shown favourable effects on concerns about falls, perceived control over falling and daily activity, after at least 8 months of follow-up. In addition, significantly fewer recurrent fallers were observed in this group after 14 months of follow-up [15]. Notwithstanding these positive outcomes, approximately 40% of the participants attended less than five sessions out of a total eight, mainly because of health problems [21]. It seems that, in particular, frail older people refrained from attending the group programme. This is also seen in other group programmes that explicitly address concerns about falls, and target frail older people living in the community [18,22].

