### Randomisation

Participants were assigned to the programme or the no-treatment control group directly after the baseline measurement using stratified randomisation. This randomisation was performed in blocks of two on the basis of one prognostic factor: the level of concern about falls (some, regular, often, and very often). Computerised alternative allocation was used in the randomisation process, which was performed by an external agency.

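### The per-protocol analysis selects only the intervention arm on attendance after randomisation, so its test is not protected by randomisation and can be biased, plausibly towards the programme

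*Protocol article*

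**What the plan says.** The Analysis section gives two principles for the effect evaluation: "Data of the effect evaluation will be analysed according to both the intention-to-treat and per-protocol principles". Of intention-to-treat it says: "In the first analyses all participants will be included according to their original assignment". For the per-protocol set the only criterion is attendance: "Participants of the intervention group who attended at least five of the seven programme sessions will be included in the per-protocol analysis". It names no criterion for controls. Under Randomisation the comparator is described thus: "Participants were assigned to the programme or the no-treatment control group directly after the baseline measurement using stratified randomisation". Controls therefore have no sessions on which they could be selected.

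The models adjust for "concerns about falls, age, gender, perceived general health, and number of falls in the past 6 months at baseline". The sentences on the mixed-effects models and on the one-tailed 0.05 significance level draw no distinction between the two analyses, so both lead to a significance test.

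The Background section reports, for the earlier group programme, that "approximately 40% of the participants attended less than five sessions out of a total eight, mainly because of health problems", and adds: "It seems that, in particular, frail older people refrained from attending the group programme". The Data collection section says that programme participants who do not comply are still approached at every follow-up, and that facilitators complete a registration form for each participant.

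**The concern.** Attendance is decided after randomisation. Dropping low attenders from one arm leaves the other arm's counterparts in place: the controls who would also have attended fewer than five sessions, had they been offered the programme, stay in the comparison. If these people have a worse outlook, the intervention arm looks better with no help from the programme.

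The listed covariates are all measured at baseline. They can remove the part of the imbalance that they capture, but not a decline in health after randomisation that makes a person stop. The Discussion section also notes that physical performance and motivation were not tested, and both could plausibly drive attendance as well as outcome. At stake is a planned test of the primary outcomes whose error rate is 0.05 only if attenders and non-attenders have the same prognosis.

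**Working it through.** **Inputs from the protocol article.** Target difference 3.8 FES-I points, SD 11.4, one-tailed alpha 0.05, power 80%, 112 per arm, 20% dropout, 140 per arm to enrol (Sample size and power). Enrolled: 389, about 194 per arm (Discussion); allocation is 1:1, since "This randomisation was performed in blocks of two" (Randomisation).

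**The plan's own figure.** n per arm = 2 × (1.645 + 0.842)² × (11.4/3.8)² = 2 × 6.18 × 9 ≈ 111.3, so 112, with power 0.802. Then 112/0.8 = 140. Both stated figures reproduce.

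**Assumptions, not in the documents.**
- The programme has no effect.
- A share p of people attend five or more sessions: 0.6 (borrowed from the group programme) or 0.8.
- Non-attenders score D × 11.4 points worse on FES-I than attenders, where D is what remains after the covariates: 0 to 0.5.
- All controls are retained, the one-sided test is directed at benefit, and the comparison is made at one time point with SD 11.4.

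**Formulas.**
- Bias = (1 − p) × D × 11.4
- Variance among attenders = 11.4² − p(1 − p)(D × 11.4)²
- SE = √[variance among attenders/(p × n) + 11.4²/n]
- False-positive rate = 1 − Φ(1.645 − bias/SE)

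**One case in full** (n = 112, p = 0.6, D = 0.33). Bias = 0.4 × 0.33 × 11.4 = 1.50 points, which is 40% of 3.8. Variance among attenders = 129.96 − 0.24 × 3.76² = 126.6. SE = √(126.6/67.2 + 129.96/112) = 1.74. Rate = 1 − Φ(1.645 − 0.86) = 0.217.

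**Bias in FES-I points**

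| p | D = 0 | 0.1 | 0.2 | 0.33 | 0.5 |
|---|---|---|---|---|---|
| 0.8 | 0 | 0.23 | 0.46 | 0.75 | 1.14 |
| 0.6 | 0 | 0.46 | 0.91 | 1.50 | 2.28 |

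**One-sided false-positive rate**

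| n per arm | p | D = 0 | 0.1 | 0.2 | 0.33 | 0.5 |
|---|---|---|---|---|---|---|
| 112 | 0.8 | 0.050 | 0.066 | 0.087 | 0.120 | 0.176 |
| 112 | 0.6 | 0.050 | 0.083 | 0.130 | 0.217 | 0.373 |
| 194 | 0.8 | 0.050 | 0.072 | 0.102 | 0.152 | 0.240 |
| 194 | 0.6 | 0.050 | 0.096 | 0.168 | 0.305 | 0.537 |

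A simulation with 20,000 runs per case agrees: 0.220 for n = 112 and 0.305 for n = 194 at p = 0.6, D = 0.33, and 0.049 and 0.050 at D = 0. The rate rises with the sample size because the bias stays fixed while the SE shrinks.

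**The case against.** **A valid comparison is already planned.** Intention-to-treat is listed first, and the follow-up of non-compliers supports it. This stands. A reader might infer from the two analyses being listed side by side that the per-protocol result could carry the main claim. The article does not say so, and a ranking of analyses may well be given in the full protocol or analysis plan, which are not shown. The point rests on the one-arm rule, which is stated.

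**The direction of bias is not established.** A reader might infer that those removed are the sicker people and that every health-related outcome leans towards the programme. The evidence comes from a different programme with weekly group sessions. The in-home version uses three home visits and four telephone calls, and was designed for people whose health kept them from a group. Everyone enrolled already rates their health as fair or poor. Entry was also widened to people with only some concern and avoidance, some of whom may stop because they feel little need, and that would push the bias the other way. The article has no in-home attendance data. So the direction is plausible, not certain.

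**That all controls stay in is an inference.** It is the natural one, since they have no sessions, but it is not written.

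**The sizes rest on assumed inputs.** The prognosis gap has no source in the article. Adjustment for baseline concerns, perceived health and previous falls may leave only a small gap, and for that reason D starts at 0 and is defined as what remains after adjustment. Loss to follow-up can also shrink the bias. If the 20% dropout in both arms came wholly from would-be non-attenders, 40% non-attendance becomes (0.40 − 0.20)/0.80 = 25% of those evaluable. With 389 × 0.8/2 ≈ 155 per arm and D = 0.5, the bias is then 0.25 × 0.5 × 11.4 = 1.43 points and the rate about 0.27. At 20% non-attendance the bias disappears.

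**The complier analysis has an assumption of its own.** Table 1 shows that the first four sessions already contain the DVD, work on unhelpful thoughts and action plans, so one to four sessions may well have an effect. This stands and is carried into the fix.

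**Conclusion.** The concern holds in limited form. The stated rule selects one randomised arm on behaviour after randomisation, so the per-protocol test does not have the protection of randomisation, and baseline covariates cannot fully restore it. The upper end of the illustrated range needs 40% non-attendance, a 0.5 SD residual gap and 194 evaluable per arm. The lower end (a bias of 0.23 points, a rate of 0.066) needs 20%, 0.1 SD and 112. Those inputs are assumptions, and the tables show what may happen, not what this trial will find. The documents do not support saying that the bias must favour the programme, or that the trial's conclusion depends on this analysis. Because intention-to-treat is kept, this is an inexpensive improvement to a supporting analysis and not a flaw in the trial's main comparison.

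**What to change.** 1. State in the Analysis section that conclusions rest on the intention-to-treat analysis.
2. For the effect of attending five or more sessions, use a complier-average causal effect analysis with randomised arm as instrument (two-stage least squares or equivalent), the same baseline covariates and all randomised participants.
3. State its assumption that fewer than five sessions has no effect. If partial attenders gain an effect e, the estimate becomes the effect in attenders plus e × (1 − p)/p, which adds 0.67e at p = 0.6 and 0.25e at p = 0.8. It would then be inflated.
4. If the per-protocol comparison is kept, label it supportive and non-randomised.

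The cost is a little more analysis work. Attendance can be taken from the facilitators' records, and non-compliers are already approached for follow-up, so no new data collection is needed. Intervals widen: the standard error is roughly that of intention-to-treat divided by p, so about 1/0.8 = 1.25 to 1/0.6 = 1.67 times as large. As a test of no effect it adds essentially nothing to intention-to-treat. Its value is an estimate of the effect of attendance that keeps the randomised comparison.

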## Methods/Design

### Design

The study concerns a two-group randomised controlled trial with a baseline measurement and follow-up measurements after 5 (directly after the programme) and 12 months (see Figure 1). The selection of potential participants was performed between March and December 2009 in four consecutive cycles. Each cycle lasted about 15 months and included: screening for eligible participants; baseline measurement; stratified randomisation; the intervention period; and follow-up measurements. The Medical Ethics Committee of the Maastricht University/Academic Hospital Maastricht in The Netherlands approved this trial.

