#### Primary outcome measures

The primary outcomes of the effect evaluation are concerns about falls and the avoidance of activity as a result of these concerns. Concerns about falls are assessed by the 16-item Falls Efficacy Scale-International (FES-I). Participants are asked to indicate how concerned they are about falling while carrying out several activities of daily living (1 = not all concerned to 4 = very concerned) [33,34]. In addition, when people indicate that they are at least somewhat concerned about falling while carrying out an activity, people are asked to indicate to what extent they avoid the activity as a result of their concerns (FES-IAB; AB indicates Avoidance Behaviour; 1 = never to 4 = often).

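### Two unranked primary outcomes are tested at two follow-ups, each at one-tailed 0.05, with no lead test or success rule, although the trial was sized on a single FES-I comparison

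*Protocol article*

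**What the plan says.** All references are to the protocol article.

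- **Outcomes.** Primary outcome measures: "The primary outcomes of the effect evaluation are concerns about falls and the avoidance of activity as a result of these concerns". Table 2 lists the FES-I and the FES-IAB together under the primary heading, unranked. An FES-IAB item is asked only when the person reports at least some concern on the matching FES-I activity.
- **Time points.** Design: "follow-up measurements after 5 (directly after the programme) and 12 months". Neither is called primary.
- **Tests.** Analysis: mixed-effects regression is used "to test for between-group differences with respect to the primary, secondary and tertiary outcome measures at all follow-up assessments".
- **Level.** Analysis: "The level of statistical significance will be set at 0.05 (one-tailed"). One level serves every outcome.
- **Sizing.** Sample size and power: "Sample size calculations are based on outcomes of a previous study using the Falls Efficacy Scale-International (FES-I"). "Two times 112 participants will provide 80% power at alpha 0.05 (one-tailed") for a difference of "at least 3.8 points (SD is 11.4 equivalent with an effect size of 0.33 on the FES-I"). The FES-IAB has no sample size calculation, and the time point of the FES-I difference is not given.
- **Use of the result.** Future implementation says that the programme can be offered to people unable or unwilling to join the group version if the trial shows effectiveness and feasibility. It does not say what would count as effectiveness.

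**The concern.** The sample size describes a trial decided by one comparison. The analysis section describes one with two primary outcomes and two follow-ups, all at the full level. The article does not connect the two.

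Two things are at stake. If one positive primary result is enough, the chance of wrongly declaring the programme effective exceeds the stated 5%. And a mixed result, such as a benefit on FES-IAB at 5 months only, could be called success or failure once the data are known. An effect directly after the programme and an effect at 12 months also support different claims.

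**Working it through.** **1. The plan's own figure.** Inputs from Sample size and power: difference 3.8, SD 11.4, one-sided alpha 0.05 (z = 1.645), power 80% (z = 0.842).

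n per arm = 2 × (1.645 + 0.842)² × (11.4 / 3.8)² = 2 × 6.18 × 9 = 111.3, so 112. With "a dropout rate of 20% during the study is expected", 112 / 0.80 = 140. Both stated figures reproduce exactly, for one outcome tested once.

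**2. Number of primary tests.** Two outcomes × two follow-ups = 4, if each follow-up has its own contrast. If the mixed model yields one longitudinal group test per outcome, there are 2. The wording allows both readings.

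**3. Chance of at least one false positive, any-one-test rule.** Independent tests: 1 − 0.95⁴ = 18.5% for four and 1 − 0.95² = 9.75% for two. For correlated tests the chance is 1 − P(all Z < 1.645) under a multivariate normal. For four tests, r is the correlation between outcomes at one time point and between time points for one outcome; for different outcomes at different time points it is r × r. The article gives no correlations, so r is assumed.

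| r | Four tests | Two tests |
|---|---|---|
| 0 | 18.5% | 9.75% |
| 0.5 | 15.0% | 8.8% |
| 0.6 | 13.9% | 8.4% |
| 0.7 | 12.6% | 8.0% |
| 0.8 | 11.1% | 7.5% |
| 0.9 | 9.2% | 6.8% |

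The two-test column also applies if FES-I is taken as the lead outcome but tested at both follow-ups.

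**4. All-must-succeed rule.** If all four tests had to be significant, the false-positive chance could not exceed 5%. Power would change instead. If each test had 80% power, independent tests would give 0.80⁴ = 41% for success. Positive correlation raises this, but it reaches 80% only if the four tests are in effect one.

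**5. Power under the remedies.** Power = Φ(3.8 / (11.4 × √(2/n)) − z). The first term is 2.494 at n = 112. Discussion reports 389 enrolled; with 20% dropout, 389 × 0.80 / 2 ≈ 155 per arm, where the first term is 2.934.

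| Level for the FES-I test | z | 112 per arm | 155 per arm |
|---|---|---|---|
| One-sided 0.05 (lead test in a fixed sequence) | 1.645 | 80.2% | 90.1% |
| One-sided 0.0125 (first Holm step over four tests, 0.05/4) | 2.241 | 60.0% | 75.6% |
| Two-sided 0.05 | 1.960 | 70.3% | 83.5% |

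The Holm row is the strictest case: the threshold eases once another test has been rejected.

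**The case against.** **The article is condensed.** A hierarchy or adjustment may stand in a fuller protocol or analysis plan, and the article never says that there will be none. This stands in part. A reader might infer that the trial's main conclusion has no error control anywhere; the article cannot show that. But it does state the two primaries, testing at all follow-ups and a single 0.05 level, and anyone following that text would run several full-level primary tests.

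**The any-one-test rule is not in the text.** This stands. The aims name concerns and avoidance as two effects to determine, and requiring every test to succeed would remove the inflation. The error rates must therefore be stated as conditional. The need for a rule remains, because under the all-must-succeed reading the stated 80% is not the power for success.

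**Four tests may be two.** This stands as a possible reading. The error rate then falls to about 7% to 10%, still above 5%.

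**Independence is implausible.** This stands. FES-IAB items depend on FES-I answers, and the same people are measured twice. The 18.5% figure is an upper bound, not an expected value.

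**Conclusion.** The point holds as a conditional one. The article fixes two unranked primary outcomes and tests them at all follow-ups at one-tailed 0.05, while its sample size supports one FES-I comparison. If any one significant primary test is read as effectiveness, the false-claim rate is about 9% to 15% for four tests at assumed correlations of 0.9 to 0.5, no more than 18.5%, and about 7% to 10% for one test per outcome. It exceeds 5% at every correlation examined.

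A reader might go further and say that the trial's false-positive rate is 12% to 19%. The documents do not support that as a flat statement. It presumes the any-one-test rule and four separate tests, its top end needs independence, and it omits the lower values that strong correlation would give. No stated figure in the sample size section is wrong. The defect is that the route from primary results to a conclusion is left open. The per-protocol analysis, planned alongside intention-to-treat, is not counted here.

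**What to change.** Before the group comparison is analysed:

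1. Name FES-I, the outcome used for sizing, at one time point chosen by the investigators as the lead test.
2. Test the remaining primary comparisons in a stated fixed order, each at the trial's one-sided 0.05, and end confirmatory claims at the first non-significant step. Holm over the primary tests is an alternative.
3. State what result will count as showing effectiveness, and whether each outcome has one longitudinal test or a contrast at each follow-up.
4. Label secondary and tertiary outcomes as supportive.

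**Cost.** This takes a few sentences and no extra participants. The article expects results in 2012 and does not say whether the groups had already been compared; if they had, a ranking added afterwards should be reported as such. In a fixed sequence the lead test keeps its 80% power at 112 per arm, or about 90% with 389 enrolled and 20% dropout. Holm costs power: 60% and about 76% respectively for FES-I at its strictest step. An effect seen only on a later-ranked comparison may become supportive only.

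A move to two-sided 0.05 is a separate question and is not needed for this fix. It would lower power to about 70% at 112 per arm, or 83.5% at about 155 per arm.
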